### Data Safety and Monitoring Board

Due to the low risk associated with study participation, no interim analyses are planned to evaluate for potential harm related to the intervention and a Data Safety and Monitoring Board is not convened.

### Sample size calculation

This study is designed to detect a 25% relative reduction in the primary outcome, the composite rate of 30-day readmission and mortality, which is reasonable given prior literature suggesting that between 22% and 42% of hospital readmissions after sepsis are preventable, including data from a secondary analysis of the subgroup of sepsis patients in our previous transitions of care trial (relative risk = 0.49, 0.24–0.97) [33]. Based on the historical data, the control group is estimated to have a 40% combined readmission and mortality rate. Group sample sizes of 354 in the STAR group and 354 in the usual care group achieve 80% power (α = 0.05) to detect a 10% absolute reduction between the group proportions (i.e., 25% relative reduction). Under the alternative hypothesis, the proportion in the STAR group is assumed to be 30%.

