**Methods:**

The Improving Morbidity during Post-Acute Care Transitions for Sepsis (IMPACTS) study is a pragmatic, randomized controlled trial at three hospitals within a single healthcare delivery system comparing clinical outcomes between sepsis survivors who receive usual care versus care delivered through the Sepsis Transition and Recovery (STAR) program. The STAR program includes a centrally located nurse navigator using telephone counseling and electronic health record-based support to facilitate best-practice post-sepsis care strategies for patients during hospitalization and the 30 days after hospital discharge, including post-discharge review of medications, evaluation for new impairments or symptoms, monitoring existing comorbidities, and palliative care referral when appropriate. Adults admitted through the Emergency Department with suspected infection (i.e., antibiotics initiated, bacterial cultures drawn) and deemed, by previously developed risk-stratification models, high risk for readmission or death are included. Eligible patients are randomly allocated 1:1 to either Arm 1, usual care or Arm 2, STAR. Planned enrollment is 708 patients during a 6-month period. The primary outcome is the composite of all-cause hospital readmissions and mortality assessed 30 days post discharge. Secondary outcomes include 30- and 90-day hospital readmissions, mortality, emergency department visits, acute care-free days alive, and acute care and total costs.

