**Fig. 1 Fig1:**
[figure not shown]
Patient flow diagram for participation in THE IMPACTS trial. The study population includes adults presenting to the Emergency Department (ED) who meet the following inclusion criteria: ≥ 18 years of age; oral or parenteral antibiotic or bacterial culture order within 24 h of ED presentation and either culture drawn first, antibiotics ordered within 48 h or antibiotics ordered first, culture ordered within 48 h; not discharged from the hospital at the time the daily list of eligible patients is generated each weekday morning; and deemed high risk for either 30-day readmission or mortality using risk-scoring models applied daily to real-time clinical data on acute and chronic factors. Patients are excluded based on receipt of prophylactic antibiotics only, hospital transfers, “do not resuscitate” or “do not intubate” (DNR/DNI) code status, distance of residence from treating hospital, and prior study randomization. Patients who have infection ruled out prior to hospital discharge are also excluded. *IMPACTS* Improving Morbidity during Post-Acute Care Transitions for Sepsis, *STAR* Sepsis Transition and Recovery

Patients are excluded if they: receive antibiotics only as part of pre-operative prophylaxis; transfer from other acute care hospitals; have a code status documented as “do not resuscitate” or “do not intubate” within 24 h after admission (due to the general assumption of increased risk of exposure to less aggressive treatment); reside > 2.5 h drive time from the treating hospital (due to the maximum reach of the community paramedicine services leveraged within the STAR program and the general assumption that these patients may have less comprehensive utilization tracking within AH record systems for study outcomes); or have been previously randomized as part of this study. Because we initially identify patients with suspected infection in order to intervene with high-risk patients in near real time, we will re-evaluate eligibility based on infection status at the time of hospital discharge. Specifically, patients who have had an infection diagnosis ruled out during their hospitalization will be excluded for the purposes of analysis (i.e., rule-out documented in medical record, assessed by blinded, adjudicated chart review for both arms). All remaining eligible patients at the time of discharge will be included in analyses.

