### Treatment allocation

Eligible patients are randomly allocated 1:1 to receive usual care or the STAR program using a computer-based randomization tool and maximally tolerated imbalance procedure with up to 10% allowable deviation to maintain similar comparison group sizes while limiting predictability of future treatment assignments [41]. Allocation concealment is achieved as the randomization is a fully automated process. However, it is not feasible to blind clinicians or patients to treatment. Due to resource limitations that allowed for only one full-time STAR navigator, the total daily number of patients randomized is constrained to include up to six patients each weekday (from the daily list of eligible patients, sorted by time of presentation). The randomization constraint is reevaluated on a biweekly basis and adjusted as needed to match the STAR navigator’s capacity.

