### Statistical analysis

Primary analyses will follow an intent-to-treat approach such that patients will be analyzed based on the group to which they were initially randomized after exclusion of patients with infection ruled out during their hospitalization. We will assess the balance in the distributions of baseline covariates for patient factors (e.g., age, comorbidities), acuity (e.g., organ dysfunction, mechanical ventilation), length of stay, and discharge disposition (e.g., SNF, rehabilitation, home) between study groups. Comparisons of the two groups will be made using univariate analyses such as the *t* test and chi-square test.

The primary composite outcome, 30-day readmission and mortality, will be compared between the two arms using logistic regression. We will present the effects of the STAR program on the incidence of the composite readmission and mortality outcome as odds ratios and 95% confidence intervals. In addition to the primary intent-to-treat analysis, and since there is significant overlap between general AH Transition Services and the STAR program services integrated within AH Transition Services, we will conduct a modified intent-to-treat analysis excluding usual care patients who attended the AH Transition Services clinic during the 30 days after hospital discharge. Based on historical data, we anticipate an approximately 10% referral rate to AH Transition Services in the usual care group. Finally, we will complete a per-protocol analysis to compare patients in the STAR intervention arm who are eligible at hospital discharge and complete the 30-day STAR program to patients who are eligible at hospital discharge and receive usual care.

Secondary acute care and cost outcomes and process measures will be evaluated using the same approach. We will test different distribution parameters to determine the optimal distribution family for each model and outcome variable (e.g., gamma distribution for costs, Poisson distribution for acute care-free days). Any substantial changes to the study processes will be documented, discussed with investigators at monthly meetings, and incorporated into analyses of study outcomes. All hypothesis tests will be two sided and data will be analyzed using SAS Enterprise Guide v7.1 (Cary, NC, USA).

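### The 80% power needs all 708 enrolled patients in the analysis, but the primary analysis drops infection rule-outs and nothing is added to replace them

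*Protocol article*

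**What the plan says.** The Abstract (Methods) sets the recruitment target: "Planned enrollment is 708 patients during a 6-month period".

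The Sample size calculation attaches power to the same total: "Group sample sizes of 354 in the STAR group and 354 in the usual care group achieve 80% power". It assumes that "the control group is estimated to have a 40% combined readmission and mortality rate", with 30% under STAR and α = 0.05. The Statistical analysis section adds that "All hypothesis tests will be two sided".

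Under Risk scoring and recruitment and Treatment allocation, patients come from a weekday list of people still in hospital with suspected infection and are randomised 1:1. Study setting and population then says that "patients who have had an infection diagnosis ruled out during their hospitalization will be excluded for the purposes of analysis", on the basis of blinded, adjudicated chart review in both arms. Statistical analysis applies that exclusion to the primary intention-to-treat comparison.

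The article gives no expected rule-out rate and no allowance for one. Missing data deals only with how completely outcomes are captured.

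**The concern.** The number to be enrolled and the number needed in the analysis are the same, yet the plan removes randomised patients between the two. Rule-outs are clearly expected. The Discussion describes the infection criteria as deliberately broad, and a chart review is set up in both arms to find patients without infection. The article gives a figure of about 10% for a different exclusion, usual-care patients seen by Transition Services in the modified intention-to-treat analysis. It gives none for the exclusion that acts on the primary analysis.

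The power figure affects how the result will be read. The Discussion says null findings would point hospital resources toward other strategies. That inference depends on the chance of missing a true 10-point reduction, which the protocol implies is 20%. If the analysed set is smaller than 708, the chance is higher.

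**Working it through.** **Inputs.** From Sample size calculation: control 40%, STAR 30%, α = 0.05, 354 per arm, 80% power. From Statistical analysis: two-sided tests. From Treatment allocation: 1:1. From the Abstract: 708 enrolled. The rule-out share *d* is not in the document; it is an assumption, taken as equal in both arms.

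**1. Reproduce the stated figure.** Normal approximation for two proportions, with z = 1.960 and 0.8416:

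- Unpooled variance: n = (1.960 + 0.8416)² × (0.40×0.60 + 0.30×0.70) / 0.10² = 7.849 × 0.45 / 0.01 = 353.2, so 354 per arm. Power at 354 is 80.1%.
- Pooled variance under the null (mean proportion 0.35, 2×0.35×0.65 = 0.455): n = (1.960×√0.455 + 0.8416×√0.45)² / 0.10² = 355.9, so 356 per arm. Power at 354 is 79.8%.

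The protocol's 354 is therefore the unpooled answer rounded up, with no inflation inside it. A continuity-corrected calculation gives 376 per arm and a one-sided one 281; neither matches.

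**2. Power if 708 are randomised and a share *d* is removed.** With n = 354(1 − d) per arm and the pooled formula,

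power = Φ[(0.10 − 1.960×√(0.455/n)) / √(0.45/n)].

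At d = 10%, n = 318.6: (0.10 − 1.960×0.03779)/0.03758 = 0.690, and Φ(0.690) = 75.5%.

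| Ruled out (assumed) | Analysed per arm | Power | Randomised in total to keep 354 per arm analysed |
|---|---|---|---|
| 0% | 354 | 79.8% | 708 |
| 2% | 347 | 79.0% | 724 |
| 5% | 336 | 77.7% | 746 |
| 10% | 319 | 75.5% | 788 |
| 15% | 301 | 73.1% | 834 |
| 20% | 283 | 70.5% | 886 |
| 30% | 248 | 64.6% | 1012 |

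The last column is twice 354/(1 − d) rounded up; for example 354/0.90 = 393.3, so 394 per arm and 788 in total. Power passes below 78% at a rule-out share of about 4.5% to 5%. A Wald approximation for the log odds ratio, closer to the planned logistic model, runs about 0.3 points lower throughout (79.5% at 0%, 75.2% at 10%, 70.1% at 20%).

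**3. The alternative of analysing everyone randomised.** Suppose 10% are rule-outs, STAR has no effect in them, and their event rate is also 40%. The STAR rate becomes 0.90×30% + 0.10×40% = 31%. Power for 40% versus 31% at 354 per arm is 70.7%, about 71%.

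**The case against.** The strongest reply is that the quoted sentence is a true conditional: groups of 354 do give 80% power for 40% versus 30%. It speaks of group sizes and not of patients randomised, and Study setting and population frames the rule-out as a re-check of eligibility at discharge. On that reading, 708 might be the number still eligible. Nor is a stop at 708 randomised written down. Six patients per weekday over roughly 130 weekdays would allow about 780, and Trial status expects recruitment to run to the end of 2019, well beyond six months from the January start. Exclusion also requires a documented rule-out, which may be uncommon; the rate could be in the full protocol; and a null result will in any case be read from the confidence interval.

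Part of this stands. The arithmetic of the sentence is correct, and the fault lies in using its answer as the enrolment target. The size of the loss cannot be known from the article and may be negligible.

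The rest does not remove the point. No sentence says that 708 counts patients left after rule-out, and the Abstract calls it enrolment. The daily cap is a limit set by navigator capacity and, like the longer recruitment window, sets no higher target. If 708 did mean analysed patients, the randomisation target would be unstated and the Abstract would mislead, so a correction is needed either way. This is also more than detail left to a fuller document, because the two numbers the article does print conflict with the analysis set it defines. The confidence interval will show the precision achieved, but the design's stated chance of detecting the effect would still be too high.

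**Conclusion.** The concern holds. With 708 enrolled as written, the primary analysis will contain fewer than 708 patients, and the design has less than the stated 80% power by an amount the protocol does not address. The shortfall against the 79.8% obtained by the pooled formula is about 2 points at 5% rule-outs, 4 at 10% and 9 at 20%. The chance of missing a true 10-point reduction at 10% to 20% rule-outs is then about 25% to 30%, not 20%.

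These sizes rest on an assumed rule-out rate, equal exclusion in both arms, and the 40% and 30% event rates applying among the patients who remain. If rule-outs are below about 4.5%, the loss is about two points or less and has little practical weight. The direction does not depend on the assumed rate, because 354 per arm leaves no margin. This should be corrected, but it does not undermine the design.

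**What to change.** State in the Sample size calculation whether 708 is the number randomised or the number analysed, and word the Abstract to match.

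- **If 708 is the number randomised:** restate power at the expected analysed number, with the rule-out rate taken from historical data or from the blinded pooled count. Example, with 10% purely as illustration: 708 randomised, about 10% ruled out, about 637 analysed, power about 76%.
- **If 708 is the number analysed:** say so, and give the randomisation target as 708/(1 − d), rounded up within each arm, for the expected rate d.
- **If all randomised patients become the primary population:** keep 708, but state the diluted effect and its power, about 71% under the 10% assumptions above.

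The first option costs one restated and slightly less favourable figure, with no extra patients and no unblinding. Trial status describes the trial as still recruiting, so the restatement can be made before results are known.

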### Missing data

We do not anticipate substantial missing data because all outcomes are routinely collected variables and utilization is broadly captured within our large integrated system. Values for patients who do not have healthcare utilization or mortality records during the study follow-up interval are assumed to be null. While utilization may occur outside AH, this is not expected to be a major limitation because of the AH market share and accessibility. Specifically, AH operates three large hospitals in Cabarrus and Mecklenburg Counties and more than 40 hospitals in the region overall. Additionally, any utilization occurring outside the system is anticipated to be non-differentially distributed between groups and thus to impact treatment groups equally. Further, internal historical data indicate that nearly 75% of high-risk patients are Medicare-insured (i.e., Medicare Shared Savings Plan beneficiaries). For these patients, we will have complete healthcare claims within and outside AH facilities during the study interval, as captured through participation in the local AH-managed Accountable Care Organization. We will conduct subgroup analyses within this Medicare-insured population and will use these data to explore missing data patterns that can be adjusted using pattern-mixture methods in sensitivity analyses.

## Discussion

The IMPACTS trial evaluates a multifaceted, patient-centered transitional care program for sepsis survivors that focuses on addressing both their immediate post-discharge needs as well as the long-term challenges in managing the downstream effects of sepsis. The intervention centers on a sepsis nurse navigator who aims to empower the patient or caregiver to manage the patient’s health condition beyond the intervention period. Evidence of an effective intervention and real-world implementation does not currently exist to guide health system decision-making and investments aimed at improving morbidity and mortality in sepsis survivors. Upon completion, this trial will provide comprehensive data on the effectiveness of delivering best-practice post-sepsis care through proactive care coordination to improve outcomes for high-risk patients. Results demonstrating better clinical outcomes for patients in the STAR program would provide evidence that structured care coordination integrated into robust transitions programs can be a useful strategy to improve the immense long-term healthcare burden of sepsis, while null findings would suggest that hospital resources may be better directed toward evaluating other post-sepsis care strategies to improve patient outcomes.

We considered several potential study design approaches while planning the IMPACTS trial. Ultimately, we concluded that a pragmatic, patient-level, randomized clinical trial was the most feasible and appropriate evaluation strategy. One central element in our decision-making process was our determination that a patient-randomized approach would not be subject to substantial unplanned cross-over that could bias outcome results. Specifically, physicians will not be able to direct usual care patients to the STAR program because this process will be determined through our automated list generation and randomized allocation. The STAR program will not accept physician referrals during the study interval. Additionally, we determined that the pragmatic design would effectively leverage our robust data systems and objective collection of clinical and outcomes data to facilitate a rigorous, real-world evaluation of post-sepsis care.

We intentionally developed broad infection criteria to initially define adults with suspected serious infection or sepsis, with the additional application of our high-performing risk stratification models to objectively narrow the population to those at the highest risk of poor outcomes and with the potential to benefit most from added support. We anticipate that this approach will include a representative sample of patients with different chronic and acute problems. Because of the expected heterogeneity, we have defined a priori several subgroups of interest to further evaluate possible differential effects of the STAR program (e.g., patients with high comorbidity burden).

There are some limitations to this study. The results may not be generalizable to all sepsis survivors because study participants are enrolled from a single healthcare system. However, the inclusion of three heterogeneous hospitals within the healthcare system increases the applicability of our findings. Second, we did not protocolize the usual care arm, thus care provided to patients in this group may be variable or change over time. While this may increase noise in determining the true treatment effect, it is consistent with the concept of a pragmatic study design. The STAR program was developed in partnership with a multidisciplinary team of sepsis stakeholders and designed to be implemented and evaluated in a real-world setting. If effective, this program would offer a timely solution for hospitals facing potential financial penalties for higher-than-expected readmission rates and looming alternate payment models such as bundled payments and shared savings programs for Accountable Care Organizations, which creates incentives to deliver care in less intensive settings during the 90 days after hospitalization.

### Trial status

The IMPACTS trial is an ongoing pragmatic randomized controlled trial evaluating clinical outcomes data for adult patients who receive care through the STAR program versus usual care during and after hospitalization for suspected sepsis. The first patient was enrolled on January 28, 2019. Protocol version 1.0 was applied (date December 17, 2018). Recruitment is anticipated to be completed by the end of 2019.

## Data Availability

Datasets generated during the current study will not be shared.
